#### Placebo

At present, there is no standard treatment in FD. Thus, the placebo for this trial requires no active components. Although Bansasin granule^® ^is not a chemical drug and relevant drug packagings may be needed for succeeding blinding, drug packaging, such as starch capsules, will not be used for reproducing the real situation of Bansasin granule^® ^administration in this trial. Therefore, mimicking the original color and taste of the Bansasin granule^® ^without adding any active components was quite a difficult procedure. The company that makes the Bansasin granule^® ^was experienced in making placebos of herbal extracts and they succeeded in making a Bansasin granule^® ^placebo through the development of several test samples. The placebo is a starch and lactose mixture which has a color and taste similar to the Bansasin granule^®^. Retention samples of placebo used in the current study will be kept at the Hanpoong Pharm & Food Company. At the end of the study, the question to participants whether the drugs that they have taken is real or not will be answered by themselves for evaluation of success in blinding.

### Outcome measures

#### Primary outcome

The primary outcome is the proof of BST's superiority compared with placebo in treating FD. For this purpose, the GIS scale is chosen as the primary variable [1]. The primary efficacy parameter is the change in the sum totals of the GIS scales. The GIS scale is composed of the following 10 dyspeptic symptoms: epigastric pain/upper abdominal pain, abdominal cramps, fullness, early satiety, loss of appetite, malaise, nausea, vomiting, retrosternal discomfort, and acidic regurgitation/heartburn. Symptom severity per each item will be assessed by a 5-point Likert scale: none - 0, slight - 1, moderate - 2, severe - 3, and very severe - 4. The GIS scale is very easy for participants to understand and to complete. The GIS scale will be assessed at baseline, 2 weeks, 4 weeks and 6 weeks during oral administration of BST, and at 1 month and 2 months after completion of BST administration.

#### Secondary outcomes

A visual analogue scale (VAS) will be used to determine the patient's global judgment of intensity of discomfort due to dyspepsia (ranging from 0 mm as no discomfort to 100 mm as the most intense discomfort). The VAS measurements will be performed with the same frequency as the GIS scale measurements.

The validated Functional Dyspepsia related Quality of Life (FD-QoL) questionnaire assesses FD's influence on quality of life and consists of four categories: diet (5 items), daily activity (4 items), emotion (6 items), and social functioning (6 items) [25]. FD-QoL will also be performed with the same frequency as the GIS scale measurements.

### Measurement of GMA

Gastric hypomotility and uncoordinated antral duodenal contractions in FD patients are closely associated with gastric myoelectrical dysrhythmias. These dysrhythmias arise from dysregulation of gastric slow waves, which normally occur at a frequency of 3 cycles per minute (cpm) [26].

Electrogastrogram records GMA acquired from cutaneous abdominal electrodes [27]. Although some researchers have suggested that some cutaneously acquired dysrhythmias may be artifactual in nature [28], other experiments have suggested a positive correlation between the frequencies found with cutaneous EGG recordings and myoelectrical signals acquired from gastric serosal leads [29,30].

In this study, the GMAs of the participants will be measured using surface multichannel EGG (Polygraf ID^®^, Medtronic A/S, Denmark) at baseline and at 6 weeks. This method of EGG measurement will be conducted as described previously [26]. First, the epigastric skin to be attached to the electrodes will be shaved and abraded with a sandy skin preparation jelly to reduce impedence. Four active surface electrodes will be positioned at the sites: the corpus of stomach as channel 1, proximal antrum as channel 2, distal antrum as channel 3, and pylorus region as channel 4. A ground electrode and a reference electrode will also be placed. EGG measurements will be performed in a quiet room and patients will fast over night for ≥ 8 hours. Participants will be asked not to talk and to remain as still as possible during the EGG assessment to avoid motion artifacts. Patients will undergo a 20 minute fasting (preprandial) EGG measurement in the supine position, then they will eat two scrambled medium eggs and two pieces of toasted bread with 500 ml of water as the standard solid test meal (500 Kcal). Then, postprandial EGG measurement will be conducted for 40 minutes. The percentage of slow wave coupling, the EGG dominant frequency and power, the percentage of normal gastric slow waves, the percentage of gastric dysrhythmia, and the postprandial to preprandial power ratio will be assessed.

### Safety

Before randomization and after completion of BST administration, we will perform the following tests on all participants: complete blood cell count, AST/ALT, γGT, BUN, creatinine, erythrocyte sedimentation rate as well as electrocardiogram. The above tests will serve to exclude participants who have serious illnesses and abnormal heart, liver, kidney, or other organ functioning. Throughout the study, we will also assess whether 6 weeks of BST administration in FD patients is safe by above tests or CRF documentations.

The guide for taking BST which are verified by the Korean Food & Drug Administration lists several adverse events: pseudoaldosteronism, myopathy, skin disorders, liver malfunction, pneumonia, or dry mouth. During the trial, all adverse events will be observed in detail and documented in case report forms (CRFs).

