**Discussion:**

This trial will provide evidence of the safety and efficacy of *Banha-sasim-tang *for the treatment for FD. Furthermore, based on the assessment of the relationship between cutaneous electrogastrography recordings and dyspeptic symptoms in this trial, the possibility of clinical applications of cutaneous electrogastrography in the treatment of FD will be elucidated.

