### Statistical analysis

The primary hypothesis is that oral administration of BST is more effective than placebo for treating FD. We hope to prove this hypothesis by means of a 2-sided test yielding a 5% significance level. Because there is no relevant previous study using BST for calculating sample size, we referred to a similar herbal trial for FD treatment which used the GIS scale [1]. The formula for estimating the sample size is as follows:

The previous trial demonstrated 3.5 points of improvement (*μ*_*c *_- *μ*_*t *_= *Δ*) in the GIS scale over treatment with placebo during 4 weeks of herbal treatments [1]. The same study indicated a mean standard deviation (SD = *σ*) of 5.37. In our study, the ratio (*λ*) of experimental group to placebo group will be 1:1. With a power of 80% (1 - β) and significance level of 5% (α), assuming Δ = 3.5 and σ = 5.37, a sample size of *n_t _*= *n_c _*= 37 patients per treatment group will be required. (*n_t_*, number of BST group; *n_c_*, number of placebo group). Considering an assumed dropout rate of 25%, a total of 100 patients will be needed.

The analysis strategy in this study is as follows:

As a first step, the baseline characteristics of both groups, sex, age, duration of dyspeptic periods, and smoking, will be compared. As a second step, we will compare the efficacy of BST and placebo, as the change in GIS totals from the beginning (0 day) to the end (6 weeks) of the study period. As a third step, we will analyze the secondary variables (VAS and FD-QoL) in the same manner as we did the GIS scale. Finally, various parameters in the EGG measurement, such as frequency and power-related variables will be compared before and after treatment in both groups. Correlations between changes in GIS scale results and EGG parameter findings will also be analyzed.

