All analyses in this study will be based on the intention-to-treat principle. If data distribution is skewed owing to insufficient sample size, relevant transformation by a statistician prior to analysis will be made. The baseline characteristics will be compared by either *χ*^2^-test or the Student *t*-test. Primary and secondary outcomes will be presented as means and SDs, and analyzed by independent *t*-tests, Mann-Whitney tests, or Wilcoxon singed-rank tests. Correlations between the GIS scale and EGG parameters will be analyzed by Pearson's correlation coefficients or by Spearman's Rho. Adverse events will be calculated and compared using *χ*^2^-test or Fisher's exact test.

Statistical analyses will be conducted in a blind manner by an independent statistician and performed using SPSS 16.0 (SPSS inc., Chicago, Illinois, USA).

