## Discussion

The current clinical study is a randomized, double-blind, placebo-controlled trial investigating the safety and efficacy of frequently used herbal formulas as part of the national project for studying the traditional herbal medicines of South Korea. This clinical trial belongs to the 2009 Traditional Korean Medicine R&D projects funded by the Ministry for Health & Welfare & Family Affairs, Republic of Korea. BST is one of the most frequently prescribed herbal formulas in Korea, BST is thought to be safe, and experimental evidences support BST's effectiveness for dyspepsia [18-20]. However, there have not been any randomized controlled trials showing the effectiveness of BST for the treatment of FD. Through the current study, we expect to gain objective clinical evidences of the efficacy and safety of BST for the treatment of FD.

The causes of functional dyspepsia are diverse and overlapping. Of the putative causes of FD, delayed gastric emptying/gastric dysmotility is one of the most important causes of FD in Korea and has been reported to closely correlate to GMA recorded by cutaneous EGG [5]. Because many researchers have suggested that cutaneous EGG could be a relatively easy technique that can be used to assess GMA in clinical settings and EGG recordings showed a significant correlation with dyspeptic symptoms in FD patients and changes in cutaneous EGG parameters in FD patients could reflect changes in their gastric motility and their dyspeptic symptoms [29,30], it is postulated that a significant correlation can be found between dyspeptic symptoms of FD patients and cutaneous EGG recordings in this trial, and the improvement in dyspeptic symptoms after the oral administration of BST may be assessed by measuring the changes in cutaneous EGG parameters. Correlations in these parameters can evaluate the possibility of clinical applications of cutaneous EGG in the treatment of FD, and a detailed guide, based on biological evidences, for treatment in FD patients.

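### The itemised safety tests include no specific marker for pseudoaldosteronism or myopathy, two listed adverse events of BST, so subclinical cases could be missed

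*Protocol article*

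**What the plan says.** The protocol article's Safety section itemises the tests done on all participants at two time points, before randomization and after BST administration ends: "complete blood cell count, AST/ALT, γGT, BUN, creatinine, erythrocyte sedimentation rate as well as electrocardiogram". It gives them two uses. One is to keep out participants with serious illness or abnormal organ function. The other is to judge whether six weeks of BST "is safe by above tests or CRF documentations".

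The section then reports that the regulator-verified guide to the product "lists several adverse events: pseudoaldosteronism, myopathy, skin disorders, liver malfunction, pneumonia, or dry mouth". Besides the fixed tests, there is a second route by which safety data are collected, since the article undertakes that "all adverse events will be observed in detail and documented in case report forms". The Statistical analysis section adds: "Adverse events will be calculated and compared using" a chi-squared or Fisher's exact test.

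Safety is a declared aim. The abstract states: "This trial will provide evidence of the safety and efficacy of" BST in functional dyspepsia. The closing Discussion repeats it: "we expect to gain objective clinical evidences of the efficacy and safety of BST for the treatment of FD".

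**The concern.** The test list and the list of known adverse events stand next to each other and do not match fully. Liver malfunction has direct markers in AST/ALT and γGT. Pseudoaldosteronism and myopathy have none: the usual laboratory signals, potassium (with the other electrolytes) and creatine kinase, are absent. Which marker belongs to which event is general clinical knowledge and is not stated in the article.

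For these two events the promised safety evidence would therefore rest on cases that someone notices, together with non-specific signals. A clean result could mean that no cases occurred, or that none became apparent. An assay not run on the scheduled samples may not be recoverable later, so the choice matters before sampling starts.

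**Working it through.** **Step 1: match the listed events to the fixed tests** (both lists from the Safety section; the matching is clinical knowledge).

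| Listed event | Specific marker in the panel | Other route |
|---|---|---|
| Liver malfunction | AST/ALT, γGT | case report form |
| Skin disorders, dry mouth, pneumonia | none; normally noticed clinically | case report form |
| Pseudoaldosteronism | none (no potassium or other electrolytes) | case report form; ECG, non-specific |
| Myopathy | none (no creatine kinase) | case report form; AST, non-specific |

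The gap is confined to subclinical cases of the last two events.

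**Step 2: the plan's own figure.** Inputs from Statistical analysis: difference 3.5, SD 5.37, two-sided 5%, power 80%. n = 2 × (1.960 + 0.842)² × 5.37² / 3.5² = 36.95, so 37 per group. Then 37 / 0.75 = 49.3, so 50 per group and 100 in total. This reproduces the article: "Considering an assumed dropout rate of 25%, a total of 100 patients will be needed". The point does not depend on it. It supplies 50 BST patients, of whom 50 × 0.75 = 37.5, taken as 37, would reach the post-treatment sample.

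**Step 3: chance of recording at least one case, for illustration.** Let p be the incidence and s the share of cases detected. Both are assumptions, because the article gives neither. The formula is 1 − (1 − p·s)^n. The marker columns take s = 100%, that is, every case abnormal at the single 6-week sample, so they are ceilings.

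| p | Case report form, n = 50, s = 25% | Same, s = 50% | Marker ceiling, n = 37 | Marker ceiling, n = 50 |
|---|---|---|---|---|
| 2% | 22.2% | 39.5% | 52.6% | 63.6% |
| 5% | 46.7% | 71.8% | 85.0% | 92.3% |
| 10% | 71.8% | 92.3% | 98.0% | 99.5% |

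Example: p = 5%, s = 25%, n = 50 gives 1 − (1 − 0.0125)^50 = 46.7%.

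With markers in 37 patients and case report forms only in the other 13, at p = 5%: 1 − 0.95^37 × (1 − 0.05·s)^13 = 87.3% (s = 25%) to 89.2% (s = 50%).

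**Step 4: what a clean result could exclude** (no incidence needed, but s is still assumed). One-sided 95% upper limits with no case recorded:
- apparent cases, 50 patients: 1 − 0.05^(1/50) = 5.8%;
- all cases, by dividing by s: 11.6% (s = 50%) to 23.3% (s = 25%);
- cases present at 6 weeks, normal markers in 37 patients: 1 − 0.05^(1/37) = 7.8%.

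If every case is clinically apparent (s = 100%), the markers add nothing.

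**The case against.** The article states nothing false here. It never says that the panel is meant to detect the six listed events, and it places those events beside the case report form route. It does not describe how adverse events are observed. Examination, vital signs or extra tests on suspicion may stand in the full protocol, and an article commonly leaves such procedures to it. The product is regulated and given at its regular dose, so how much laboratory monitoring it needs is a clinical judgement. The figures in the working follow from assumed inputs. They compare a marker ceiling with a case report form route that gives the ECG and AST no separate credit, and they ignore false positives.

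Much of this stands. A reader might infer that subclinical cases would certainly go undetected. The documents do not support that, because the ECG, AST and case report forms give partial detection. A reader might also take the probabilities as the size of the problem. They cannot show it, since neither incidence nor the apparent share is given. Nor is the missing mention of blood pressure raised here, because vital signs are the kind of detail a full protocol holds.

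What does not stand is that the panel is merely abbreviated. The article does not refer to routine laboratory tests and leave the rest open. It itemises the tests for all participants and makes them one of two grounds for judging safety. If the full protocol does include the two assays, a one-line clarification settles the matter.

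**Conclusion.** The point holds as a cheap improvement to a fixed test list that fits the product's listed risks poorly. Subclinical pseudoaldosteronism and myopathy could be missed, while clinically apparent cases are covered. The conclusion rests on the two lists in the Safety section and on ordinary clinical knowledge of which markers fit which event.

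Its size is unknown. The illustrative contrast ranges from no gain, if all cases are apparent, to 47-72% against 85-92% at an assumed 5% incidence with 25-50% apparent. A reader might go further and conclude that the safety evidence as a whole is unsound, or that the main result is at risk. Neither follows: the other four listed events are not at issue, and the efficacy analysis and sample size are untouched.

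**What to change.** Add serum electrolytes including potassium, and creatine kinase, to the two blood draws already scheduled, and report abnormal values by arm. The placebo arm then shows the background rate of incidental abnormalities. If the assays are not added, state that the safety conclusion for these two events covers clinically apparent cases only.

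Cost: two routine assays in at most 100 × 2 = 200 samples (about 100 + 75 = 175 with 25% dropout), some incidental abnormal values to follow up, a minor amendment and no new visit. The alternative costs one sentence.

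Limits: a single post-treatment sample misses transient changes and patients who leave before it. Clinical handling of abnormal values is for the investigators.

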### Quality control

Before starting the trial, investigators who assess the EGG will receive thorough training in taking EGG measurements.

To maintain the accuracy and quality of the clinical trial, audit and monitoring will be conducted by the Marinet Corporation, a CRO located in Seoul, Korea. The sites' CRF completion and compliance with standard operation procedures will be audited. Clinical research associates will, at regular periods, monitor the clinical trial procedures such as compliance with BST administration and voluntary withdrawal of participants. In particular, reasons for withdrawal will be fully documented in CRFs.

### Statistical analysis

The primary hypothesis is that oral administration of BST is more effective than placebo for treating FD. We hope to prove this hypothesis by means of a 2-sided test yielding a 5% significance level. Because there is no relevant previous study using BST for calculating sample size, we referred to a similar herbal trial for FD treatment which used the GIS scale [1]. The formula for estimating the sample size is as follows:

The previous trial demonstrated 3.5 points of improvement (*μ*_*c *_- *μ*_*t *_= *Δ*) in the GIS scale over treatment with placebo during 4 weeks of herbal treatments [1]. The same study indicated a mean standard deviation (SD = *σ*) of 5.37. In our study, the ratio (*λ*) of experimental group to placebo group will be 1:1. With a power of 80% (1 - β) and significance level of 5% (α), assuming Δ = 3.5 and σ = 5.37, a sample size of *n_t _*= *n_c _*= 37 patients per treatment group will be required. (*n_t_*, number of BST group; *n_c_*, number of placebo group). Considering an assumed dropout rate of 25%, a total of 100 patients will be needed.

The analysis strategy in this study is as follows:

As a first step, the baseline characteristics of both groups, sex, age, duration of dyspeptic periods, and smoking, will be compared. As a second step, we will compare the efficacy of BST and placebo, as the change in GIS totals from the beginning (0 day) to the end (6 weeks) of the study period. As a third step, we will analyze the secondary variables (VAS and FD-QoL) in the same manner as we did the GIS scale. Finally, various parameters in the EGG measurement, such as frequency and power-related variables will be compared before and after treatment in both groups. Correlations between changes in GIS scale results and EGG parameter findings will also be analyzed.

All analyses in this study will be based on the intention-to-treat principle. If data distribution is skewed owing to insufficient sample size, relevant transformation by a statistician prior to analysis will be made. The baseline characteristics will be compared by either *χ*^2^-test or the Student *t*-test. Primary and secondary outcomes will be presented as means and SDs, and analyzed by independent *t*-tests, Mann-Whitney tests, or Wilcoxon singed-rank tests. Correlations between the GIS scale and EGG parameters will be analyzed by Pearson's correlation coefficients or by Spearman's Rho. Adverse events will be calculated and compared using *χ*^2^-test or Fisher's exact test.

Statistical analyses will be conducted in a blind manner by an independent statistician and performed using SPSS 16.0 (SPSS inc., Chicago, Illinois, USA).

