### Randomization

Randomization will be controlled by an independent clinical research coordinator (CRC). First, the randomization form with the basic information of the participant who has passed the screening phase will be transmitted in facsimile to the independent statistician. The randomization number in the randomization form will be left blank before arrival to the statistician. The statistician will then decide the randomization number based on the allocation sequence which has been generated by a random number creation program in advance and the statistician will return the randomization form filled in with the established number (specific ID number) to the CRC. The ratio of randomization allocation to the sites will be 1:1. The CRC will inform the investigators of the specific ID number. This procedure will be guaranteed by the authorized contract research organization (CRO).

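### The primary GIS comparison tests change from baseline with no covariate; adjusting for baseline GIS would usually gain precision at almost no cost

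*Protocol article*

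**What the plan says.** The Primary outcome section of the protocol article defines the efficacy parameter as the change in the GIS total. The Statistical analysis section states the comparison as "compare the efficacy of BST and placebo, as the change in GIS totals from the beginning (0 day) to the end (6 weeks", and says VAS and FD-QoL will be analysed in the same way. It then names the methods: "Primary and secondary outcomes will be presented as means and SDs, and analyzed by independent" t-tests, Mann-Whitney tests or Wilcoxon signed-rank tests. None of these takes a covariate, and the article mentions no ANCOVA, regression or mixed model.

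The Primary and Secondary outcomes sections have GIS, VAS and FD-QoL measured at baseline and at each later assessment. A baseline value is therefore planned for every patient.

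The sample size is set for a two-arm comparison of means: "We hope to prove this hypothesis by means of a 2-sided test yielding a 5% significance level"; "With a power of 80% (1 - β) and significance level of 5% (α"; "assuming Δ = 3.5 and σ = 5.37"; and the ratio "of experimental group to placebo group will be 1:1". This gives 37 per arm, raised to 100 in total for 25% dropout.

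**The concern.** A change score subtracts the whole baseline value, which assumes that each extra GIS point at baseline carries through to one extra point at week 6. ANCOVA estimates that slope from the data. When the true slope is below 1, the change score over-corrects and its variance contains a baseline component that the model could have removed.

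Precision is what is at stake. The design targets 80% power if 25% of patients are lost to the analysis. The baseline measurement that could improve on this is already planned, and the named tests leave it out except through subtraction. The article fixes both the outcome and the tests, so this is a stated choice and not a detail left to an unseen analysis plan.

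**Working it through.** **Inputs from the Statistical analysis section.** Two-sided α = 0.05, power 80%, Δ = 3.5, σ = 5.37, ratio 1:1, dropout 25%.

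**Inputs not in the article (assumed).** The correlation r between baseline and week-6 GIS, taken as 0.3, 0.5 and 0.7; the ratio of baseline to week-6 variance; and, except in step 5, that 5.37 is the SD of change.

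**1. The plan's own figure.** n per arm = 2 × (1.960 + 0.842)² × 5.37² / 3.5² = 36.95, so 37. For dropout, 37 / 0.75 = 49.3, so 50 per arm and 100 in total. Both reproduce. At 37 per arm, power is 80.0% by the normal approximation and 79.0% by the non-central t. Steps 3 and 4 use the non-central t.

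**2. Variance under each analysis.** Let b be the slope of week 6 on baseline, Vx the baseline variance and Ve the residual variance.
- Change score: (1 − b)² × Vx + Ve
- ANCOVA: Ve

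With equal variances s² at both times, b = r. The change-score variance is then 2s²(1 − r), the ANCOVA variance is s²(1 − r²), and their ratio is (1 + r)/2.

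**3. Equal variances, 37 per arm, SD of change 5.37.**

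| r | variance ratio | reduction | residual SD | power |
|---|---|---|---|---|
| unadjusted | 1 | none | 5.37 | 79.0% |
| 0.3 | 0.65 | 35% | 4.33 | 92.9% |
| 0.5 | 0.75 | 25% | 4.65 | 89.1% |
| 0.7 | 0.85 | 15% | 4.95 | 85.1% |

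**4. Narrower baseline.** The Inclusion criteria require at least three GIS symptoms rated moderate, which may narrow the baseline range. The SD of change is kept at 5.37, and variances are in units of s².

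(a) Same slopes, baseline variance halved (Vx = 0.5, Ve = 1 − b²):
- b = 0.3: 0.91 / (0.49 × 0.5 + 0.91) = 0.788; power 87.6%
- b = 0.5: 0.75 / (0.25 × 0.5 + 0.75) = 0.857; power 84.8%
- b = 0.7: 0.51 / (0.09 × 0.5 + 0.51) = 0.919; power 82.2%

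(b) Same correlations, baseline SD 0.7 times the week-6 SD (Vx = 0.49, b = r/0.7, Ve = 1 − r²):
- r = 0.3, b = 0.43: ratio 0.850; power about 85%
- r = 0.5, b = 0.71: ratio 0.949; power about 81%
- r = 0.7, b = 1.00: ratio 1.000; power 79%, no gain

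**5. If 5.37 is the SD of a single score.** With equal variances and the normal approximation at 37 per arm, power for the change score against ANCOVA is 65.9% against 83.6% (r = 0.3), 80.0% against 89.9% (r = 0.5) and 95.1% against 97.5% (r = 0.7).

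**The case against.** The strongest reply is that nothing is broken. Under randomisation the change-score test holds its 5% level and is unbiased, and the sample size was computed for just such a two-sample comparison. This stands, and it limits the point to efficiency. Several stronger readings are tempting, and the documents do not support them.

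- **Bias from chance baseline imbalance.** An observed baseline difference d leaves (1 − b) × d in the change-score contrast. That is a conditional shift, and its spread is already in the t-test's standard error. Counting it on top of the lost variance would count one cost twice.
- **Selection on high GIS makes the change score worse.** Under a linear relation, selecting on baseline leaves the slope unchanged, and regression to the mean affects both arms alike. A narrower baseline range tends to shrink the gain, as step 4 shows.
- **No slack in the sample size.** The 79% applies only if the full 25% are lost from the analysis. The article states intention-to-treat; with all 100 analysed, unadjusted power is about 90%.
- **Arms not balanced within centre.** The Randomization section says "The ratio of randomization allocation to the sites will be 1:1", which is ambiguous, and the sample-size text gives 1:1 by arm. Stratification and blocking are details that a condensed article may leave to the full protocol, so silence here shows nothing.
- **Baseline significance tests.** The plan that "The baseline characteristics will be compared by either" a χ² or t-test does not alter the primary estimate. Baseline GIS is absent from the variables listed for that comparison, but this does not show that it will go unreported.

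The objection that the headline gain depends on unstated quantities also stands, which is why a range is given.

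**Conclusion.** The point holds as a recommendation on efficiency. It identifies no invalid test and no error in the sample size. The protocol article commits the primary and secondary outcomes to unadjusted tests of change although their baselines are collected.

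If 5.37 is the SD of change and the variances are equal, adjustment lifts power at 37 per arm from 79% to between 85% and 93% for correlations from 0.7 down to 0.3. With a narrower baseline the range is about 82% to 88% in one scenario and 79% to 85% in the other, with no gain where the true slope equals 1. In large samples the ANCOVA variance is never larger than that of the change score. The direction is therefore secure, but the size is not, because the correlation, the variance ratio and the meaning of 5.37 are not stated.

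**What to change.** Name one primary analysis: a linear model (ANCOVA) of the week-6 GIS total, or equivalently its change, on treatment and baseline GIS total, reporting the adjusted difference with its 95% CI. Analyse VAS and FD-QoL the same way, each with its own baseline. Centre may be added as a covariate for one further degree of freedom; the documents do not allow its gain to be quantified. State which quantity the SD of 5.37 describes.

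Keep N = 100, since the size of the gain is uncertain. Visits and data collection do not change. The cost is a few lines of wording and code, plus one degree of freedom for the baseline covariate. The model should be fixed before unblinding.
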